### 5.3.10 Biological examinations

#### 5.3.10.1 Nasopharyngeal swabbing

Nasopharyngeal swabbing is to be carried out upon pre-inclusion (for diagnostic purpose and not part of the trial's procedures), on Day 7 and Day 14, transported and processed in the laboratory according to a standard procedure [SDPM].

#### 5.3.10.2 Blood tests

Blood samples are to be taken on Day 0, Day 7 and Day 14 transported and processed in the laboratory according to a standard procedure [SDPM].

Blood samples are to be used thus:

- The day of sampling (on Day 0, Day 7 and Day 14): CBC, PCT, CRP, ferritin, creatinine, urea, sodium, potassium, chloride, calcium, magnesium, albumin, bicarbonates/tCO2, LDH, CPK, ASAT, ALAT on Day 0, Day 7 and Day 14.
- Remotely, on frozen plasma and kept in biobanks:
  - On Day 7 for later pharmacological examination (measurement of plasma trough concentrations of the drugs by HPLC/MS-MS)
  - On Day 0, Day 7 and Day 14 for immunological examination, if the patient has agreed to participate in the immunological sub-study [SDPM] (please see paragraph **Erreur ! Source du renvoi introuvable.**)

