### 1.3.4 Favipiravir

Favipiravir is an antiviral selectively inhibiting the RNA dependent RNA polymerase of the numerous viruses, including influenza, hantaviruses, flaviviruses, arenaviruses, filoviruses, bunyaviruses and enteroviruses (49,50). Its evaluation in the treatment of Ebola virus disease during the epidemic that occurred in West Africa was judged to be non-conclusive in terms of efficacy (51) yet allowed improvements to knowledge of its pharmacokinetics among patients afflicted by a severe viral infection (52). The mechanism of action of favipiravir make it a credible candidate for evaluation in the context of COVID-19. Favipiravir is currently being evaluated in the context of 7 clinical trials for COVID-19. Various brief reports containing non-published data from China and Japan have declared that the preliminary results obtained with favipiravir for COVID-19 patients have been encouraging (53). The preliminary data of a clinical trial suggesting that favipiravir would reduce the duration of viral excretion and improve radiological results in patients infected by SARS-CoV-2 has been communicated in an informal manner by a Shenzhen hospital. Favipiravir at an initial dose of 1,600mg followed by 600mg thrice daily is recommended as an alternative option for patients suffering from COVID-19, who are intolerant of lopinavir/ritonavir among Chinese recommendations (24). On the basis of knowledge of pharmacokinetics of the molecule obtained from the Ebola epidemic (52,54) and of not yet data published regarding the antiviral action of favipiravir in vitro on SARS-CoV2, a regimen using higher doses of favipiravir would have better chances of allowing the attainment of therapeutic concentrations doses among patients suffering from COVID-19. In this trial, we have chosen to use that dose already used during the Ebola epidemic, higher than the dose recommended for influenza in Japan, but already administered under close clinical monitoring in humans.

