#### 5.4.2 Description of expected adverse events

Expected adverse events for the trial's drugs are those specified in the Summary of Product Characteristics (SPC) for Plaquenil®, Imatinib TEVA®, Avigan® and Micardis®.

The Summary of Product Characteristics (available online on the trial eTMF) provides the complete list and the level of risk for each drug. The risks of adverse reactions for the 4 experimental drugs for short treatments of 10 days are slim. Adverse reactions, whether the most frequent (even if they are benign) or the most serious (even if they are rare) are as follows:

- Hydroxychloroquine: abdominal pain, diarrhoea, nausea, vomiting, lengthening of the QT interval and *torsades de pointes* or ventricular tachycardia, hypersensitivity, medullar aplasia, pruritus, rash, headache and hypoglycaemia.
- Telmisartan: rash, orthostatic hypotension, cardiac decompensation, hypersensitivity and elevation of transaminases.
- Imatinib: cardiac decompensation, elevation of transaminases, neutropenia, thrombocytopenia, anaemia, pancytopenia, headache, dyspnoea, cough, abdominal pain, vomiting, nausea, diarrhoea, cramps and water retention.
- Favipiravir: elevation of transaminases, diarrhoea, nausea, vomiting, headache, hyperuricemia and hypertriglyceridemia.

Any adverse event, neither appearing in the list of expected events, nor in the latest version of the benchmark document, is deemed to be unexpected.

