#### 5.4.3 Conduct to be maintained by the researcher in the case of adverse event or new finding

##### 5.4.3.1 Reporting of adverse events (AE)

The researcher is responsible for reporting adverse events occurring between the date of signature of consent and the end of the participant's participation, apart from those detected before the first application of the trial's treatment. If the clinical or biological adverse event is present at the time of signature of consent, only its deterioration needs to be recorded.

In the context of this protocol, all adverse events must be reported.

The researcher is to record adverse events (clinical and biological) in the observations log. Such adverse events are researched upon every visit over the course of the study by the posing of questions and during the participant's clinical examination.

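### The Day 0, 7 and 14 blood panel has no uric acid or triglyceride assay, so two of the three laboratory reactions the protocol names for favipiravir have no scheduled detection and no baseline

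*Protocol*

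**What the plan says.** Section 5.3.10.2 states which assays are done on the day of sampling at Day 0, Day 7 and Day 14. The list begins "CBC, PCT, CRP, ferritin, creatinine, urea, sodium, potassium, chloride, calcium, magnesium, albumin", then gives bicarbonates/tCO2, and ends "LDH, CPK, ASAT, ALAT on Day 0, Day 7 and Day 14". The reference there to a separate procedure concerns transport and processing of the samples, not the choice of analytes. Frozen plasma has two stated uses: "measurement of plasma trough concentrations of the drugs by HPLC/MS-MS" at Day 7, and immunology for those who join the optional sub-study.

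Section 5.4.2 picks out, for each drug, the reactions that are most frequent or most serious. For one drug it reads "Favipiravir: elevation of transaminases, diarrhoea, nausea, vomiting, headache, hyperuricemia and hypertriglyceridemia". For hydroxychloroquine the list ends "medullar aplasia, pruritus, rash, headache and hypoglycaemia".

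On recording, section 5.4.3.1 says "The researcher is to record adverse events (clinical and biological) in the observations log". It looks for events by questioning and examining the participant at each visit, and it records a condition already present at consent only if it worsens. Section 4.3.2 makes the number and proportion of graded adverse events and adverse reactions, by group from Day 0 to Day 14, secondary outcomes. Section 6.3.7 analyses safety on available data.

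**The concern.** The protocol names certain biochemical reactions as worth listing, requires biological events to be recorded and reports graded events by arm, yet its assay list leaves some of those reactions unmeasured. Raised uric acid and raised triglycerides usually cause no symptoms over a ten-day course, so questions and examination will seldom reveal them.

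The missing Day 0 value matters as well. Because an event present at consent counts only if it worsens, a raised value found by chance during follow-up could not be classed as new or pre-existing. Eligibility does not supply a baseline either: section 5.1.2.4 excludes symptomatic gout or hyperuricemia as reported by the person, not as measured.

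The gap is also uneven between drugs, and it falls hardest on favipiravir. Section 1.3.4 says that drug is given at a dose "higher than the dose recommended for influenza in Japan". Tolerance is a secondary objective (section 3.2), and no later analysis can recover a value that was never measured.

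**Working it through.** No formula or stated figure is at issue. The check sets the reactions in section 5.4.2 that a blood test would show beside the assays in section 5.3.10.2.

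**Step 1: the panel.** The first run holds 12 entries, bicarbonates/tCO2 is 1 more, and LDH, CPK, ASAT and ALAT are 4 more: 12 + 1 + 4 = 17. None is uric acid, triglycerides or glucose.

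**Step 2: match by drug.**

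| Drug | Laboratory reaction named in 5.4.2 | Assay in 5.3.10.2 |
|---|---|---|
| Favipiravir | raised transaminases | ASAT, ALAT |
| Favipiravir | hyperuricemia | none |
| Favipiravir | hypertriglyceridemia | none |
| Hydroxychloroquine | medullar aplasia | CBC |
| Hydroxychloroquine | hypoglycaemia | none |
| Imatinib | raised transaminases | ASAT, ALAT |
| Imatinib | neutropenia, thrombocytopenia, anaemia, pancytopenia | CBC |
| Telmisartan | raised transaminases | ASAT, ALAT |

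Coverage: favipiravir 1 of 3, hydroxychloroquine 1 of 2, imatinib 5 of 5, telmisartan 1 of 1.

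**Step 3: other routes to detection.**
- Remote visits on Days 1, 3, 5, 9 and 12 (section 5.3.5), face-to-face visits on Days 7 and 14 (5.3.6), unscheduled calls (5.3.7) and the end-of-trial visit (5.3.8) can bring out symptoms such as those of gout or hypoglycaemia.
- A value measured in usual care or in hospital can be recorded as a biological event.
- Neither route looks systematically for a silent change, and neither gives a Day 0 value.

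**Step 4: what extra assays could catch.** The drugs concerned are taken from Day 0 to Day 9 (sections 5.2.2 and 5.2.4). Day 7 is on treatment. Day 14 is 14 − 9 = 5 days after the last dosing day. At full size an arm such as favipiravir would hold 169 + 53 = 222 participants, which gives at most 222 on-treatment samples and 222 × 2 = 444 post-baseline samples. Both are ceilings. Section 5.3.9 allows Day 7 and Day 14 visits to become remote, with their samples omitted, and the 53 is an expectation that section 6.2.2 does not fix in advance.

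**Step 5: size of the under-count.** It would be the number treated, times the rate of each reaction, times the share that stays silent. The protocol gives neither of the last two, so no figure can be computed.

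**The case against.** The strongest reply is that listing a reaction as expected does not commit a protocol to assay for it. Section 5.4.2 lists reactions that are frequent even when benign, or serious even when rare, describes the risks of a ten-day course as slim, and leaves the level of each risk to the product summaries. Section 5.4.3.1 asks that events be recorded, not that each expected one be sought by a blood test. A narrow panel is a reasonable choice for an emergency trial run in people's homes. All of this is fair, and it means there is a mismatch between two sections and not a breach of either. It does not remove the mismatch, since the panel already covers every laboratory reaction named for two of the four drugs.

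Two stronger readings are tempting and are not supported.

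- A reader might infer that these reactions cannot be detected at all. The contacts in Step 3 and usual-care results can bring some to light; what goes unseen is silent change.
- A reader might infer that the favipiravir and hydroxychloroquine arms will look falsely safe. The three analytes are unmeasured in every arm, control included, so the trial is uninformative on these items. Transaminases, blood counts, ECG findings and symptoms are still collected for both drugs. How the monitoring board would read the counts is speculation.

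The objection is strongest for hypoglycaemia. It is transient and often symptomatic, and a single glucose value on Day 7 and another after treatment has ended would seldom catch an episode.

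**Conclusion.** The point holds as a misalignment between sections 5.3.10.2 and 5.4.2. Asymptomatic hyperuricemia and hypertriglyceridemia, two of the three laboratory reactions named for favipiravir, have no scheduled means of detection and no baseline, while the laboratory reactions named for imatinib and telmisartan are all covered. The graded adverse event outcomes will under-count these two items and cannot inform on them. A side-by-side reading of laboratory events across drugs should allow for that. Hypoglycaemia is a lesser instance of the same gap.

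The conclusion assumes that the assay list is complete as printed and that the unnamed procedures add no analytes. The sample ceilings in the working describe opportunity to measure, not harm missed. The primary outcome is unaffected. This is an inexpensive improvement to safety ascertainment and not a threat to the trial's main result.

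**What to change.** In section 5.3.10.2, add uric acid and non-fasting triglycerides to the Day 0, Day 7 and Day 14 assays in all arms, and grade the results as biological adverse events in the same way as the other assays. All arms are needed so that ascertainment is equal and the control arm gives a reference.

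Glucose may be added on the same samples. Whether or not it is, state that hypoglycaemia is captured mainly when symptomatic or found incidentally, because single values detect it poorly.

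If the panel is not extended, section 5.4.2 or 6.3.7 should say that these reactions are captured only when symptomatic or incidental and that the laboratory adverse event comparisons do not cover them.

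The cost is two or three routine assays on blood already drawn at those visits (10 ml each in Table 1), with no extra visit or venepuncture. The drawbacks are a small laboratory charge and some noise from non-fasting triglycerides. No dose, eligibility rule or treatment rule changes.

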### 3.2 Secondary objectives

The study's secondary objectives are:

- Appraise the efficacy of several experimental treatments of SARS-CoV-2 infection, compared with standard of care, to prevent death on Day 28
- Appraise the efficacy of several experimental treatments of SARS-CoV-2 infection, compared with standard of care, to prevent hospitalisation on Day 28
- Appraise the efficacy of several experimental treatments of SARS-CoV-2 infection, compared with standard of care, to prevent admission to intensive care unit on Day 28
- Appraise the efficacy of several experimental treatments of SARS-CoV-2 infection to eliminate nasopharyngeal carriage of the virus, compared with standard of care
- Appraise the efficacy of several experimental treatments of SARS-CoV-2 infection, compared with standard of care, to prevent loss of autonomy
- Appraise tolerance of experimental treatments against SARS-CoV-2 infection
- Study those factors associated with clinical deterioration in patients with COVID-19
- Evaluate the feasibility and acceptability of the trial and model of care model implemented.
- Evaluate the relationship between concentrations for each drug and efficacy of each of the treatments

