#### 4.3.2 Secondary criteria

- Hospitalisation proportion and its causes between Day 0 and Day 28 within each group
- Proportion of deaths and their causes between Day 0 and Day 28 within each group
- Intensive care hospitalisation proportion and its causes between Day 0 and Day 28 within each group

---

 Currently, the following criteria are being proposed: SpO2 < 92% in ambient air or 4% reduction in SpO2 since inclusion; respiratory rate > 30 min; heart rate > 130/min; systolic blood pressure < 90 mmHg or diastolic < 60 mmHg; other parameters indicating hospitalisation, in the judgement of the attending physician (for example, unexplained fall, severe digestive problems, reoccurrence or persistent fever > 38.5°C etc.)

- Proportion of patients with a reversion of SARS-CoV2 RT-PCR on a nasopharyngeal swab on Day 7 and Day 14, in each group
- Proportion of patients with a loss of autonomy evaluated by ADLs and IADLs on Day 14 and Day 28
- Changes in CBC, inflammatory markers (please see paragraph **Erreur ! Source du renvoi introuvable.**) and immunological markers (please see paragraph **Erreur ! Source du renvoi introuvable.**) from Day 0 to Day 7 and Day 14 in each group
- Number and proportion of adverse events of grades 1, 2, 3, 4 between Day 0 and Day 14 in each group
- Number and proportion of adverse reactions of grades 1, 2, 3, 4 between Day 0 and Day 14 in each group
- Plasma trough concentration of experimental drugs in the study on Day 7
- Acceptability of the treatment

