#### 5.2.3 Imatinib

- Brand name: Imatinib TEVA®
- 400 mg per tablet
- 1 tablet *QD* from Day 0 to Day 9 (Day 0: at any time after inclusion; from Day 1 to Day 9: to be taken at 08:00 am)
- To be kept below 25°C

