#### 5.3.4 Remote monitoring of the ECG and consideration of the blood electrolytes for inclusion

- People in receipt of an ECG device are to take a reading 3-4 hours after the morning treatment intake on Day 1, then daily 3-4 hours after it up to Day 7. The ECG shall be transmitted remotely. The ECG shall be read directly by the on-call cardiologist. In the event of any anomaly, requiring a stop to the trial's drug, the person shall be informed by telephone and receive a visit from the mobile team.

The device shall be recovered by the mobile team on Day 7.

- The kalaemia dosed on the inclusion sample shall be made available to the researchers on the same day of inclusion. In the event of severe hypokalaemia, the researcher shall contact the attending physician for corrective measures. If the confirmed figure indicates the trial drug should be interrupted, provisions shall be made by telephone with the person, the attending physician and the mobile team, so that the decision can be enacted immediately.

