#### 5.3.6 Face-to-face visits (Day 7 and Day 14)

- Face-to-face visits shall be carried out in the participant's home by the trial's mobile team.
- Face-to-face visits are to consist of:
  - Interview and clinical examination (including the recording of undesired effects)
  - Taking of drugs
  - SpO2
  - Blood sampling
  - Nasopharyngeal swab for SARS-CoV2 RT-PCR
  - Advice

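### The Day 7 plasma trough is not tied to any dose, and the fixed 08:00 imatinib intake makes any later Day 7 draw a post-dose sample

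*Protocol*

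**What the plan says.** **The endpoint and its purpose.** Section 4.3.2 lists as a secondary criterion "Plasma trough concentration of experimental drugs in the study on Day 7". Section 3.2 gives the objective it serves: "Evaluate the relationship between concentrations for each drug and efficacy of each of the treatments". Section 5.3.10.2 assigns Day 7 frozen plasma to this assay ("On Day 7 for later pharmacological examination (measurement of plasma trough concentrations of the drugs by HPLC/MS-MS") and names no other day for pharmacology.

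**The draw.** Section 5.3.6 places the Day 7 blood sample at a home visit: "Face-to-face visits shall be carried out in the participant's home by the trial's mobile team". It gives no hour and no pre-dose condition. Its list of visit content covers drug intake in general terms, without naming the time of the last dose or of the sample. The procedure cited in section 5.3.10.2 concerns samples being "transported and processed in the laboratory according to a standard procedure [SDPM".

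**The doses.** Imatinib has a clock time (section 5.2.3): "from Day 1 to Day 9: to be taken at 08:00 am". Hydroxychloroquine (5.2.2) and telmisartan (5.2.5) are once daily from Day 1, and favipiravir (5.2.4) is twice daily. None of these three has a clock time.

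**The ECG device.** For participants who have one, section 5.3.4 puts the first reading 3-4 hours after the Day 1 morning intake, "then daily 3-4 hours after it up to Day 7". It adds: "The device shall be recovered by the mobile team on Day 7".

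**The concern.** A trough is the level just before the next dose. A sample drawn at an unspecified point in the dosing interval is a different quantity, and calling it a trough does not change that. If the dose-to-draw interval varies between participants and is not recorded, visit time enters the exposure variable as measurement error. That tends to flatten any relation between concentration and efficacy. Post-dose levels read as troughs also overstate minimum exposure.

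The loss could not be repaired later. Day 7 is the only pharmacological sample, and treatment ends on Day 9, before the Day 14 blood draw. Section 9.3.2 says that, apart from laboratory results, patient data go straight into the e-CRF and have no source record. A clock time not captured at the visit could not be looked up afterwards.

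**Working it through.** The plan states no figure on this point. The check is clock arithmetic on its stated times.

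**1. Imatinib, all participants.** Inputs: dose at 08:00 on Day 7 (5.2.3); draw at a visit on Day 7 (5.3.6, 5.3.10.2).
- A pre-dose sample requires the draw by about 08:00.
- A draw later on Day 7 is (clock time − 08:00) hours post-dose. The range is 0 h to 24:00 − 08:00 = 16 h.
- Time left to the next dose is 24 − (hours since dose), so at least 24 − 16 = 8 h.

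If the 08:00 instruction is followed, no Day 7 visit after 08:00 gives a trough.

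**2. The other three drugs.** No dose time and no visit time are stated, so the interval can only be bounded:
- hydroxychloroquine and telmisartan, once daily: 0 to 24 h;
- favipiravir, twice daily: 0 to 12 h, assuming doses 12 h apart.

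**3. ECG-device subset.** Suppose a reading is taken on Day 7, the device is collected after it, and blood is drawn at the same visit. The draw is then at least 3-4 h after the morning intake:
- once daily: at most 24 − 4 = 20 to 24 − 3 = 21 h before the next dose;
- favipiravir (12 h spacing assumed): at most 12 − 4 = 8 to 12 − 3 = 9 h before it.

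The protocol states none of those three steps as a sequence.

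**4. Illustration of size.** Half-lives are not in the protocol, so a range is assumed, with first-order elimination and instantaneous absorption. For a sample t hours post-dose in an interval of τ hours:

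ratio to trough = 2^((τ − t)/half-life)

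| Assumed half-life | t = 4 h, τ = 24 h: 2^(20/half-life) | t = 4 h, τ = 12 h: 2^(8/half-life) | 3 h against 10 h post-dose: 2^(7/half-life) |
|---|---|---|---|
| 6 h | 10.1 | 2.5 | 2.2 |
| 12 h | 3.2 | 1.6 | 1.5 |
| 24 h | 1.8 | 1.3 | 1.2 |
| 48 h | 1.3 | 1.1 | 1.1 |

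The 24 h column does not apply to favipiravir; the 12 h column does, under the spacing assumption. The last column is the spread due to visit time alone. These ratios show how far timing could matter. They are not estimates for any trial drug.

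**5. Order of sample and event.** Section 4.3.1 counts hospitalisation or death from Day 0, while the level is taken on Day 7. For an event before the draw, exposure is either missing or measured after the outcome. This matters only if the Day 7 level is related to that endpoint.

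**The case against.** The strongest reply is that the protocol never says when the Day 7 visit takes place. Section 5.2.3 fixes the imatinib dose, not the visit, and a team arriving before 08:00 would draw a true trough. That stands. A reader might infer that the Day 7 levels are not troughs anywhere in the trial, and the text does not support that.

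A reader might also take the ECG timings to show a visit at 11:00-12:00 or later. They do not. The device goes only to participants with a borderline QTc or another cardiac risk factor (5.3.3). Section 5.1.2.2 limits this monitoring to the first seven days of treatment, which could end on Day 6 when treatment starts on Day 0. Table 1, with its footnotes 3 and 4, separately provides a Day 7 ECG by the mobile team with no delay after dosing. The timings suggest a post-dose visit in that subset and prove nothing for the others.

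Next, section 1.1 leaves roll-out details to separate procedures, and neither these nor the e-CRF are shown. It is therefore not established that intake and draw times go unrecorded. This reply is weaker than it looks, because the reference in section 5.3.10.2 names transport and laboratory processing, not the time of sampling. It also leaves the conflict between the 08:00 intake and a Day 7 trough unresolved.

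Section 3.2 does not say which efficacy measure the level will be related to, and section 6.3.1 leaves the detail of secondary analyses to the SAP. The protocol cannot be said to plan an analysis of Day 7 levels against earlier events, so that part is conditional advice. Likewise, section 1.3.4 argues for the favipiravir regimen from therapeutic concentrations and names no target trough. Nothing here undermines that choice.

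**Conclusion.** The point holds in a limited form. The protocol names a Day 7 trough but contains nothing that makes the draw pre-dose. For imatinib, its own dosing instruction makes any Day 7 draw after 08:00 post-dose, by up to 16 hours. For hydroxychloroquine, telmisartan and favipiravir, the time since dose cannot be derived from the text. In the ECG-device subset the timings point towards a post-dose visit without establishing it.

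The imatinib conclusion assumes only that participants take the dose when told to. The favipiravir bounds assume doses 12 hours apart, and the fold differences rest entirely on assumed half-lives.

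The consequence is confined to one secondary criterion and one secondary objective. The Day 14 primary endpoint, the sample size and the stopping rules are untouched. It is worth correcting because the correction is cheap and the single on-treatment sample cannot be repeated.

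**What to change.** Reconcile sections 4.3.2 and 5.3.10.2 with sections 5.2.3, 5.3.4 and 5.3.6, without changing any dosing time:

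- Record on the e-CRF the clock time of the last intake before the draw and the clock time of the Day 7 draw.
- Define the criterion as Day 7 plasma concentration with time since last dose. Use the word trough only for samples within a stated pre-dose window.
- If Day 7 levels are related to hospitalisation or death, count only events after the sample.

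The cost is two e-CRF fields and a reworded endpoint. The result becomes a time-adjusted concentration, which is less simple to report than a trough. Under the third step, events before Day 7 leave the concentration-efficacy analysis, which reduces its event count.
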